### Exploratory analysis

Descriptive analyses will be performed to provide information related to the study's experience conducting the initial screening patients within their primary care clinics.

Data from initial screens will be utilized to provide a greater description of the patient population at screening, recruitment and enrollment (e.g., race; ethnicity; preferred language; age; gender; level of depression (i.e., PHQ-2 score); service utilization, as well as identify which of these variables, if any, served to influence participation in the study. This information will allow us to describe, for example, whether consent to be contacted differs by level of depression and whether this is moderated by demographic factors (e.g., race, ethnicity, gender). Additionally we will provide additional data describing rates of enrollment as compared to the total screened.

Secondary exploratory analyses will explore the impact of the intervention on depression. Patients' scores on the QIDS-SR will be compared between the usual care and intervention arms. To measure changes in racial and ethnic disparities in depression recognition and treatment, rates of depression diagnoses will be compared from baseline to six-month follow-up for the intervention and usual care arms. As measures of the use of any ongoing specialty mental health care, the rates of prescription of pharmacotherapy and referrals/visits to mental health specialists as provided by patient self-report will be compared at baseline and at the six-month follow-up. Data analysis will be conducted using STATA statistical software [35].

A general linear model that accounts for clustering at the PCP level will be used. Analyses of the main outcomes will include as covariates any patient or physician factors that differed significantly between study arms. Outcomes regarding diagnosis and treatment will be assessed using general estimating equations with a binomial link and standard errors will be adjusted to account for clustering within practice. Separate analyses will be conducted for each outcome (i.e., dependent variables) -- changes in depressive symptoms, diagnosis of and treatment (prescription of antidepressant medications; referrals/visits to mental health specialists) for depression at six months after enrollment. The effect of study arm on each outcome will be assessed, controlling for significant differences emerging from the bivariate analyses.

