### Study Aims

This study is a randomized controlled trial of a culturally focused psychiatric consultation model for Asian American and Latino American primary care patients with depression (see Figure 1). The *primary aim *of the study is to determine the feasibility, satisfaction and cost associated with implementing a CFP consultation service within a primary care setting at MGH. Additionally, an *exploratory aim *serves to describe (e.g., demographic factors; level of depression; service utilization) the participant patient population at screening, recruitment and enrollment, as well as to determine which, if any, of these variables influence participation in the study (e.g., consent to be contacted).

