## Methods/Design

### Overview

This is a randomized controlled trial of the CFP intervention. During the study period, all patients in participating primary care clinics will receive a screening form for symptoms of depression; data on age, gender, race, ethnicity and primary language will be obtained at the time of screening. Asian American and Latino American patients who screen positive for clinical depression will be contacted by study staff and invited to participate in the CFP study. Eligible patients will be randomized either to the intervention arm or usual care based on their primary care provider. Patients in the intervention arm will receive the CFP intervention over two visits and then called at six-months by study staff to administer follow-up questionnaires (described below). Patients in the usual care arm will be called at baseline and at six-month follow-up by study staff to administer questionnaires (described below). To evaluate the cultural components of the study, a number of qualitative interviews will also be conducted with participants in the intervention and usual care arms, and with members of the target population who did not participate in the study. Please see Figure 1 for the study flowchart.

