### Randomization scheme

Primary care patients at MGH will be randomized by pods, which comprise multiple clusters of 5-6 PCPs within each practice site. Using electronic medical records data from 2007, practices will be matched based on an index composed of two variables: 1) the number of patients who are members of the target minority groups and 2) the rate of diagnosed depression. Within each pair, one practice will be randomized to participate in the intervention and the other will be assigned to the "usual care" arm.

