### Baseline Visit

Both patients in the intervention and usual care arm will give consent to participate in the study at the beginning of the baseline visit. In the intervention arm, assessment measures used at baseline to characterize the intervention patient population will include the Mini International Neuropsychiatric Interview (MINI) [28], Quick Inventory of Depressive Symptomatology-Self Rated Scale (QIDS-SR) (see Appendix 2) [29], Global Assessment of Functioning (GAF) [21], and Schwartz Outcome Scale (SOS-10) [30]. Questionnaires regarding the patients' demographics and utilization of resources will also be assessed. In the usual care arm, for target minorities who screen positive, the assessment measure will include the QIDS-SR and SOS-10.

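### The analysis of who participates does not name study arm, although arm is set before consent and the two arms are offered different things

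*Protocol article*

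**What the plan says.** **The participation analysis.** Study Aims sets an exploratory aim of describing patients at screening, recruitment and enrolment, "as well as to determine which, if any, of these variables influence participation in the study (e.g., consent to be contacted"). Exploratory analysis repeats it: the data will "identify which of these variables, if any, served to influence participation in the study". The variables listed are race, ethnicity, preferred language, age, gender, PHQ-2 score and service utilization. The worked example asks "whether consent to be contacted differs by level of depression and whether this is moderated by demographic factors (e.g., race, ethnicity, gender"). The denominator is undivided: "we will provide additional data describing rates of enrollment as compared to the total screened". Arm, pod and practice are not mentioned in this part. They do enter the outcome analyses later in the same section.

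**How arm arises.** Overview: "Eligible patients will be randomized either to the intervention arm or usual care based on their primary care provider". Randomization scheme: "Primary care patients at MGH will be randomized by pods, which comprise multiple clusters of 5-6 PCPs within each practice site". That section then describes allocation of one member of each matched pair of practices to each arm.

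**When patients consent, and to what.** Baseline Visit puts consent at the same point in each arm: "Both patients in the intervention and usual care arm will give consent to participate in the study at the beginning of the baseline visit". Intervention patients are offered the consultation, the toolkit and a two-week follow-up (Description of Intervention). For the other arm, Overview says: "Patients in the usual care arm will be called at baseline and at six-month follow-up by study staff". Usual-care patients are offered the intervention at the end of the study (Definition of Usual Care). Bipolar disorder excludes patients in the intervention arm only (Inclusion/Exclusion Criteria).

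**The concern.** Enrolment here happens after allocation. A patient's arm is determined by the PCP's cluster, and the patient is then called, invited and asked to consent. Two things are at stake.

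- **Meaning of the predictors.** In the intervention arm, participation means agreeing to see a mental health clinician. In usual care it means agreeing to answer questionnaires. Only the first bears on whether this service is acceptable, which is what the feasibility aim needs. A pooled predictor averages the two.
- **Validity of the arm comparison.** If different kinds of patients enrol in the two arms, the exploratory QIDS-SR comparison is biased, even though clusters were randomized. The screening form covers patients who did not enrol as well as those who did. It is therefore the natural place to look for such selection, but only if the data are split by arm.

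**Working it through.** The plan states no figure on this point, so there is none to reproduce. All uptake rates and patient mixes below are assumptions, except the 44% acceptance of a psychiatric assessment reported under Preliminary Studies for an Asian American primary care population. That figure serves only as an anchor.

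**1. Selection that pooling hides.** Assume half of screened patients in each arm are severe and half mild, with equal numbers per arm.

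| | Severe uptake | Mild uptake | Severe share of enrolled |
|---|---|---|---|
| Intervention | 50% | 30% | 0.50/(0.50+0.30) = 62.5% |
| Usual care | 30% | 50% | 0.30/(0.30+0.50) = 37.5% |
| Pooled | (50+30)/2 = 40% | (30+50)/2 = 40% | |

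Severity shows no pooled association with participation, yet the enrolled arms differ by 25 points. In a milder version, usual-care uptake is 40% in both groups. Pooled uptake is then 45% and 35%, and the enrolled severe share is 62.5% against 50%. Neither version needs any imbalance at screening.

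**2. Strength of the planned check.** Exploratory analysis adjusts for factors that differ significantly between arms. The revised sample is 120, or 60 per arm (Sample size and power). Two-sided 5% power, ignoring clustering, is Φ((Δ − 1.96·SE0)/SE1), with SE0 = √(2·p̄(1−p̄)/60) and SE1 = √((p1(1−p1)+p2(1−p2))/60).

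- 62.5% v 37.5%: (0.25 − 1.96×0.0913)/0.0884 = 0.80, power 79%.
- 62.5% v 50%: (0.125 − 1.96×0.0906)/0.0899 = −0.58, power 28%.
- 60% v 50%: (0.10 − 1.96×0.0908)/0.0904 = −0.86, power 19%.

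The check would probably find extreme selection but would usually miss moderate selection. It also cannot compare enrolled with non-enrolled patients within an arm.

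**3. Confounding by arm.** Take a binary predictor with no effect within either arm and equal numbers screened per arm. Let its share be x in the intervention arm and 1−x in usual care, with uptake pI and pU. Pooled uptake is x·pI + (1−x)·pU with the predictor and (1−x)·pI + x·pU without it.

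| pI v pU | Mix by arm | Pooled uptake, with v without | OR |
|---|---|---|---|
| 44% v 44% | any | 44.0% v 44.0% | 1.00 |
| 44% v 30% | 50/50 | 37.0% v 37.0% | 1.00 |
| 44% v 30% | 60/40 | 38.4% v 35.6% | 1.13 |
| 44% v 20% | 70/30 | 36.8% v 27.2% | 1.56 |
| 44% v 60% | 60/40 | 50.4% v 53.6% | 0.88 |
| 44% v 70% | 70/30 | 51.8% v 62.2% | 0.65 |

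The bias needs both an uptake difference and an imbalance, and its direction depends on which arm has the higher uptake. With arm in the analysis the odds ratio is 1.00 in every row.

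**4. How large an imbalance is plausible.** Four practices take part (Target PCP practices), which is two per arm if practices are the unit. With an assumed between-cluster SD s of 5 to 15 points in the predictor share, and ignoring matching, the SD of the arm difference is s·√(1/2+1/2) = 5 to 15 points. The matching index uses the number of target-minority patients and the rate of diagnosed depression. It does not fix the Asian American to Latino American split or the language mix.

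**The case against.** The strongest reply is that this is silence in a condensed article. The section calls the work descriptive, the variable lists are introduced as examples, and no participation model or pooling rule is fixed. This stands in part: arm is unnamed, not excluded. A reader might infer that the plan fits a model that deliberately omits arm, and the text does not support that. The same section does, however, name arm and clustering for the outcome analyses, and it states a single denominator for enrolment. Followed as written, the analysis would be pooled.

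Second, the contrast in offers is softer than it looks. Recruitment strategy describes one invitation, usual-care patients are offered the intervention later, the two-week follow-up may be by phone, and the article does not say what patients know about their arm before consent. Consent to be contacted, the one participation endpoint named, may come before any arm-specific offer. All this stands for that endpoint. It does not cover enrolment, which the aim also includes. Consent is given at the start of the baseline visit, which contains the consultation in one arm and is a questionnaire call in the other. Eligibility also differs by arm.

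Third, a reader might infer that selective enrolment would go undetected. That is too strong. Enrolled arms are compared on patient and physician factors, and Qualitative analysis adds interviews with non-participants and asks usual-care participants how they understood the study when they enrolled. These checks are weak or qualitative, but they exist.

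Fourth, arm is randomized in matched pairs, so predictors are balanced in expectation. This stands, and it makes confounding the secondary argument.

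**Conclusion.** The concern holds in a limited form. The participation analysis should name arm, because enrolment follows allocation and the arms differ in offer and eligibility. The main reason is that predictors may act differently by arm: with the assumed rates above, a null pooled result can coexist with a 25-point difference in enrolled severity, and the planned check has 19% to 28% power for differences of 10 to 12.5 points at 60 per arm. Clustering would lower that further.

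Confounding by arm is possible but not shown. The odds ratios of 0.65 to 1.56 rest on assumed uptake and mix, and they return to 1.00 if either is equal across arms. A reader should not conclude that the reported predictors will be confounded, or in which direction.

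The point touches the exploratory aim, the acceptability reading and the exploratory QIDS-SR comparison. It does not affect the sample size, the cost analysis or the satisfaction measures.

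**What to change.** - Report counts of patients who screened positive, were contacted, consented and enrolled, by arm.
- Within each arm, compare enrolled with non-enrolled patients on the screening-form variables: PHQ-2 score, race and ethnicity, language, age and gender. Service utilization is not on that form (Initial Screen), so it cannot be part of this comparison unless obtained elsewhere.
- Include arm in the enrolment analysis and account for clustering. Give arm-specific estimates, or a small number of arm-by-predictor terms labelled exploratory and imprecise.
- Base conclusions on the acceptability of the consultation on the intervention arm.
- Adjust the QIDS-SR model for screening PHQ-2 score and ethnicity regardless of significance tests between arms.

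Cost: a few sentences of analysis wording and slightly more analysis work. The screening variables are already collected, and arm is known from the PCP. The interaction estimates will be imprecise and should be reported as such. No stated figure changes.

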### Six-month follow-up

Patients will have the option to complete the visit over the phone or in person. In both the intervention and usual care arms, patients will be given the QIDS-SR self-rated questionnaire and asked a brief "Resource Utilization Questionnaire" with questions regarding use of antidepressant medications, referrals/visits to mental health specialists, or alternative providers both in and out of the MGH system. The electronic medical record will also be reviewed at baseline and at the six-month follow-up for both intervention and usual care arms to obtain depression diagnoses, prescription of antidepressant medications, and referrals/visits to mental health specialists in the system.

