### Sample size and power

Initially, we planned for a total sample size of 506 patients, split evenly between the intervention and usual care groups. We calculated this sample size to yield 84 percent power to detect a difference in the reduction of depressive symptoms on the QIDS-SR by 50 percent in the intervention arm versus 35 percent in the treatment arm, paralleling the experience of patients in the intervention arm in STAR*D, an multi-center effectiveness study of Major Depression in primary care settings [31] as well as the experience of patients in usual care arm in several studies [32-34]. However, given the multiple recruitment challenges we have faced to date, we have revised our total sample size to 120 patients, split evenly between intervention and usual care groups. Although this sample size is significantly smaller, the results of both the qualitative and exploratory analyses of this study will inform further iterations of this intervention and study design.

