## Discussion

The intervention is designed to provide enhanced recognition and treatment of depression in Asian American and Latino American primary care patients, while placing minimal additional burden on the existing primary care system at MGH. Several challenges to the implementation of this intervention exist, including minimizing burden to participating sites, recruitment and retention issues, and language and literacy issues.

Regarding the first challenge, obtaining staff and partnership buy-in during the grant-writing stage, and soliciting feedback from all levels of administration during every step of the process of designing and implementing the study has been instrumental. Regular meetings with participating sites are crucial to clarify workflow, questions about the service, and other issues that may arise. Keeping the protocols simple and easy to implement will be critical.

As with any clinical research intervention, recruitment and retention (e.g., dropout, loss to follow-up) are concerns (40). This is particularly relevant for recruitment and retention of minorities. Within recruitment and retention, the CFP team will consider how and which cultural issues are applicable in order to target Asian American and Latino American primary care patients. Among these groups, examples of such characteristics may include language and literacy, use of complementary and alternative treatments, the perceived importance of the quality of interpersonal relationships between the patient and CFP team, and the relationship between the PCP practices and the CFP team.

To address language and literacy issues, all materials (e.g., consent forms, study instructions) and the CFP consultations will be provided in the patient's preferred primary language, and materials for the toolkit will be developed at a sixth-grade reading level. The patient toolkit has also been prepared in audio CD format for patients with literacy issues. Recruiting research assistants and clinical staff with Spanish, Mandarin, Cantonese and Vietnamese proficiency are crucial to the team.

If patients and providers indicate strong satisfaction with the CFP intervention, it is hoped that the intervention can be expanded through a large scale randomized controlled trial of the intervention. Findings from such a study will provide evidence for the effectiveness of this model to improve the mental health of minorities in primary care settings.

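### The prescription and referral comparison rests on self-report, so patients not reached at six months have no outcome, although a record review of the in-system items is already planned

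*Protocol article*

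**What the plan says.** Under Exploratory analysis, the treatment comparison is described with its data source: "the rates of prescription of pharmacotherapy and referrals/visits to mental health specialists as provided by patient self-report will be compared". The sentence presents these rates as measures of any continuing specialty mental health care. The modelling paragraph that follows lists antidepressant prescription and specialist referral/visit again as outcomes at six months, without naming a source.

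Under Six-month follow-up, two sources are collected:

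- The Resource Utilization Questionnaire, given to patients in both arms, asks about "use of antidepressant medications, referrals/visits to mental health specialists, or alternative providers both in and out of the MGH system". On how this visit takes place: "Patients will have the option to complete the visit over the phone or in person".
- The record: "The electronic medical record will also be reviewed at baseline and at the six-month follow-up for both intervention and usual care arms", and its purpose is "to obtain depression diagnoses, prescription of antidepressant medications, and referrals/visits to mental health specialists in the system".

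On retention, the Discussion says that "recruitment and retention (e.g., dropout, loss to follow-up) are concerns" and adds that this applies particularly to minorities. On size, Sample size and power says "we have revised our total sample size to 120 patients, split evenly between intervention and usual care groups".

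**The concern.** Antidepressant prescription and specialist referral/visit are collected twice. One source depends on reaching the patient at six months. The other does not depend on the patient answering. The analysis section names the first and does not say what the second is for.

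If that sentence is followed as written, a patient who breaks contact after baseline has no six-month value for these outcomes, even where the hospital record shows a prescription or referral. The comparison is then made among those reached. If being reached is related to having taken up care, and that relation differs between arms, the observed rates differ for reasons other than the intervention. The arms do have different contact patterns (two clinician visits against study calls), so different retention is plausible, but the article does not say in which direction. The loss also falls on a sample already reduced from 506 to 120.

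**Working it through.** The article gives no expected rate, power or dropout allowance for these outcomes. Its one power statement concerns the QIDS-SR at the superseded size of 506, so there is no plan figure to reproduce here.

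**Step 1. The two sources side by side**

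| | Self-report questionnaire | Electronic record |
|---|---|---|
| Arms | Both at six months | Both |
| Needs patient contact at six months | Yes (phone or in person) | Not stated to |
| Care covered | In and out of the system | In the system only |
| Source named in Exploratory analysis for these rates | Yes | No |

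The self-reported baseline is itself unclear in usual care. The Baseline Visit text lists only the QIDS-SR and SOS-10 for that arm, while Table 1 marks the Resource Utilization Questionnaire at baseline with no arm limit. The record review is stated for both arms at baseline.

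**Step 2. Patients left for the self-report analysis**

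Inputs: 120/2 = 60 per arm (Sample size and power); loss d is assumed, 10 to 40%, equal in both arms.

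- Remaining per arm: n = 60 × (1 − d).
- 95% half-width for a difference in rates near 50%: 1.96 × √(2 × 0.25/n). This ignores clustering, which would normally widen it.
- Width of the worst-case range for the difference when nothing is assumed about the missing: d + d.

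| Assumed loss | n per arm | Half-width (points) | Worst-case width (points) |
|---|---|---|---|
| 0% | 60 | 17.9 | 0 |
| 10% | 54 | 18.9 | 20 |
| 20% | 48 | 20.0 | 40 |
| 30% | 42 | 21.4 | 60 |
| 40% | 36 | 23.1 | 80 |

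The loss of precision is small, about 5 points at 40% loss. The uncertainty about who is missing is the larger issue.

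**Step 3. Direction of bias under no true effect (all response patterns assumed)**

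- Scenario A: true rate 40% in both arms. Intervention loses 30%, of whom 20% were treated; usual care loses 15%, of whom 30% were treated. Observed: (0.40 − 0.30 × 0.20)/0.70 = 48.6% against (0.40 − 0.15 × 0.30)/0.85 = 41.8%. Intervention minus usual care = +6.8 points.
- Scenario B: true rate 47% in both arms, an illustrative value from the chart-review study in Preliminary Studies, where (38 − 20)/38 received some intervention. In usual care, 90% of treated and 70% of untreated patients respond; in the intervention arm, 80% respond regardless. Usual care: 0.47 × 0.90/(0.47 × 0.90 + 0.53 × 0.70) = 0.423/0.794 = 53.3%. Intervention: 47.0%. Difference = −6.3 points, with nearly equal retention (79.4% against 80%).
- Scenario C: loss unrelated to treatment in either arm. Difference = 0.

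A spurious difference of 6 to 7 points can therefore arise in either direction, or not at all. Similar retention in the two arms does not rule it out.

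**The case against.** Several points on the other side stand.

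- A reader might infer that the record is never used for these outcomes. The text does not go that far. The modelling paragraph names no source, the record items are presumably collected for some analysis, and the self-report phrase could be read as applying to referrals/visits alone. What can be said is that self-report is the only source named for this comparison.
- A reader might infer that the record ought to replace self-report. It should not. The stated target is any specialty care, and the record holds only "prescription of antidepressant medications, and referrals/visits to mental health specialists in the system". Out-of-system care may also differ by arm: the intervention toolkit includes information on community resources, while usual-care PCPs receive a list of the hospital's own mental health referrals. A record-only outcome could under-count care unequally.
- A reader might infer that self-report is compromised by unblinded patients and the record is not. Intervention-arm PCPs receive the consultation recommendations and make the prescriptions and referrals, so the record is not blind either.
- The general handling of missing outcomes may be settled in an analysis plan that is not shown. That is accepted, and no finding is made on it. It does not remove the point that the article attaches this comparison to the source that needs patient contact.
- The article does not say in terms that the record is reviewed for patients who miss the six-month contact. It sets no such condition either, but the cost estimate depends on this.

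**Conclusion.** The point holds in limited form. The article names self-report as the source for the prescription and specialist referral/visit comparison. On that basis patients not reached at six months contribute no outcome, although an in-system measure of the same items is already planned in both arms.

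The size is unknown because no dropout rate is given. Under assumed losses of 10 to 40%, the self-report analysis would have 54 to 36 patients per arm instead of 60. The bias scenarios show only that the result could move several points either way. They do not support a claim that the plan favours the intervention.

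The outcomes are secondary exploratory, and the primary aim (feasibility, satisfaction and cost) is a separate matter, so severity is modest. It is still worth correcting, because the article says the exploratory results will inform later versions of the intervention and design.

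**What to change.** In Exploratory analysis, keep the self-report comparison for care in or out of the system among patients reached, and add beside it:

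1. An analysis of in-system antidepressant prescription and in-system specialist referral/visit, taken from the electronic record at baseline and six months, for every enrolled patient in both arms, whether or not the six-month contact is completed (unless consent to record review is withdrawn).
2. By arm, the number of patients with record data only, and the agreement between the two sources where both exist.
3. A statement that the two analyses measure different things (in-system care in all patients; any care in those reached), and that differences between their results will be interpreted in that light.

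In Six-month follow-up, state that the record review covers all enrolled patients. Reconcile the Baseline Visit text with Table 1 on whether usual-care patients complete the Resource Utilization Questionnaire at baseline.

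Cost: wording only, if the record review already covers everyone enrolled. If it was meant only for patients who complete the contact, the extra work is 6 to 24 record reviews per arm at assumed losses of 10 to 40%. The remaining limitation is that the record cannot show out-of-system care, and a patient who has left the system may look untreated when the truth is unknown. This is why the record analysis is added and does not replace self-report.
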